#### Sample size considerations

A CITS study requires data for a minimum of three time points pre-intervention and three time points post-intervention and must also allow for any seasonal effect on the outcomes.^56^ Monthly data will be obtained for 24 months pre-intervention and 12 months post-intervention. Consequently, for each intervention Trust, there will be 72 data points prior to introduction (24 for the intervention Trust and 48 for the control Trusts) and 36 data points post intervention (12 for the intervention Trust and 24 for the control Trusts). Sample size calculations were undertaken based on our two initial measures, CMOC for MINAP and use of non-invasive ventilation first for patients requiring ventilation for PICANet; full details are provided in online supplementary file 3.

10.1136/bmjopen-2019-033208.supp3Supplementary data

#### Analysis

Monthly MINAP and PICANet data will be extracted to spreadsheets for analysis with R software.^57^ For both NCAs, each outcome will be regressed on time and the intervention. The time component will include a seasonal effect (quarterly effect) and will allow for a (linear) time trend. To account for clustering of monthly observations within hospitals, a random intercept will be fitted, although a fixed effect for hospital as a sensitivity analysis will be explored. Although the intervention is abrupt, its impact may well be ‘phased in’ over a few months, perhaps three. The timing of the bedding in of the intervention will be reported from the multi-site case study. Then a partial effect can be considered for this period with the interaction effect stepping up in a linear fashion.

The results of the CITS analysis will be incorporated into the biography of QualDash, the analysis of the data from the multi-site case study describing how contextual factors shape the evolution of practices around QualDash and how this leads to the resulting outcome pattern.

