Given the study intention to determine the feasibility of and inform the design of a trial, a range of measures will be considered. Initially, we selected two process measures, one for MINAP and another for PICANet. For MINAP, we selected the composite process measure cumulative missed opportunities for care (CMOC). This has nine components (pre-hospital ECG, acute use of aspirin, timely perfusion, referral for cardiac rehabilitation and prescription at hospital discharge of what are considered to be the gold standard drugs—aspirin, thienopyridine inhibitor, angiotensin converting enzyme inhibitor, β-Hydroxy β-methylglutaryl-CoA (HMG-CoA) reductase inhibitor and beta blockers) and is inversely associated with mortality.^54^ As some of these components, such as pre-hospital ECG, are outside the direct control of the Trust, we will also explore the impact of QualDash on the individual measures that make up CMOC. On the basis of the measures that cardiology clinicians described in the interviews as being important for measuring care quality, we will also look at the percentage of patients who receive an angiogram within 72 hours from first admission to hospital, which is part of the Best Practice Tariff financial incentive scheme, and, for those hospitals that provide percutaneous coronary intervention (PCI), the proportion of patients who have a door-to-balloon time (the time from arrival at the hospital to PCI) of less than 60 min. Our CMO configurations (online supplementary file 2) suggest improvement will be seen in measures if: clinical teams perceive them as being important indicators of care and/or they relate to financial incentives; performance is not in line with expectations; they perceive the measure as being within their control; and the team is resourced to introduce QI initiatives in relation to these measures.

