For PICANet, we selected use of non-invasive ventilation first for patients requiring ventilation, which has been shown to be associated with reduced mortality.^55^ However, this was not raised as an area of concern in our interviews with PICU clinicians. On the basis of this and two additional considerations—it would require loading additional data into QualDash which would reduce the performance of QualDash in terms of speed and it requires computation of the data, while the focus of QualDash is on visualising the data—a QualCard has not been created for this metric. Therefore, while we will still include this measure in the CITS, we do not hypothesise that it will change, unless other sources of information, such as the PICANet annual report, draw a PICU team’s attention to it. However, accidental extubation and unplanned readmission within 48 hours were identified in our interviews with PICU clinicians as being important indicators of care quality, so we will include these two measures in the CITS. On the basis of our CMO configurations (online supplementary file 2), we would expect to see an improvement in these measures in sites where performance is not in line with expectations, if the team is resourced to introduce QI initiatives in relation to these measures.

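### Improvement is predicted only at some sites, but the CITS model as written names one intervention effect per outcome and would show no pattern across sites

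*Protocol article*

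**What the plan says.** **Predictions.** For MINAP, the CITS study section ties improvement in a measure to several conditions. They begin "clinical teams perceive them as being important indicators of care and/or they relate to financial incentives; performance is not in line with expectations" and go on to the team's perceived control over the measure and its resources for QI. For accidental extubation and 48-hour readmission in PICANet, "we would expect to see an improvement in these measures in sites where performance is not in line with expectations", again if the team is resourced. The QualDash section expects under-resourced sites to perceive more benefit. The abstract says the realist hypotheses will be tested across five hospitals, and the Setting/context section selects Trusts for variation in key outcomes.

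**Division of labour.** Under Study design, outcome data for testing the CMO configurations come from the CITS. Contexts, mechanisms and intermediate outcomes come from the case study.

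**Model.** In the CITS Analysis section, "For both NCAs, each outcome will be regressed on time and the intervention". On clustering the section adds: "To account for clustering of monthly observations within hospitals, a random intercept will be fitted", with a hospital fixed effect as a sensitivity analysis. No intervention effect that varies by site, and no context interaction, is named.

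**Matched sets.** Each intervention Trust has two matched controls, and the sample size section counts data by set: "for each intervention Trust, there will be 72 data points prior to introduction (24 for the intervention Trust and 48 for the control Trusts").

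**Phase-in.** The CITS Analysis section allows for a gradual build-up but fixes no length: "its impact may well be ‘phased in’ over a few months, perhaps three". It leaves the length to be informed by the ethnographic work, and it words the phase-in term itself as an option: "Then a partial effect can be considered for this period with the interaction effect stepping up in a linear fashion".

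**The concern.** A hospital intercept absorbs differences between hospitals in level. It does not let the effect of QualDash differ between them. The theory says that some Trusts should improve on a measure and others should not, yet a single intervention term averages the two groups. The more selective the true response, the smaller that average.

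Two things are at stake. First, objective 1 asks in what contexts QualDash leads to improvement. The case study is to explain the resulting outcome pattern, but one number per measure is not a pattern across sites. Second, the trial feasibility section uses the CITS in judging whether a trial is justified and which audits should enter it. A null result caused by averaging could count against an audit in which QualDash worked where it was expected to.

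The open phase-in is a separate and smaller matter. Its length is not fixed, its use is optional, and its timing comes from information gathered after introduction.

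**Working it through.** **The plan's own counts.** With 24 months before, 12 after and two controls per Trust: 24 × 3 = 72 points before and 12 × 3 = 36 after per matched set; 5 × 2 = 10 controls. All three agree with the article. It gives no alpha, power, effect size or SD (these are referred to supplementary file 3, not shown), so the rest is illustration.

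**Assumptions.** Residual SD 1; independent errors; equal-length series; hospital effects, linear trend, quarter, a common post-period change and an intervention-by-period term; two-sided alpha 0.05; effect d in k of n intervention Trusts and none in the others.

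**Dilution.** The pooled estimate is (k/n) × d. For 2 of 5 it is 0.40d; for 1 of 3 it is 0.33d.

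**Standard errors.** The variance of one hospital's before-after change is 1/24 + 1/12 = 0.125.
- Pooled MINAP, 5 v 10: √[0.125 × (1/5 + 1/10)] = 0.194
- Pooled PICANet, 3 v 6: √[0.125 × (1/3 + 1/6)] = 0.250
- One matched set, 1 v 2: √[0.125 × (1 + 1/2)] = 0.433

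**Power at d = 1 residual SD.**

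| Audit | k of n | Pooled estimate | Pooled z | Pooled power | Power, one responding Trust v its own controls |
|---|---|---|---|---|---|
| MINAP | 1 of 5 | 0.20 | 1.03 | 0.18 | 0.64 |
| MINAP | 2 of 5 | 0.40 | 2.07 | 0.54 | 0.64 |
| MINAP | 3 of 5 | 0.60 | 3.10 | 0.87 | 0.64 |
| MINAP | 4 of 5 | 0.80 | 4.13 | 0.99 | 0.64 |
| PICANet | 1 of 3 | 0.33 | 1.33 | 0.27 | 0.64 |
| PICANet | 2 of 3 | 0.67 | 2.67 | 0.76 | 0.64 |

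Site-specific terms in a joint model that shares all controls do better: standard error 0.371 and power 0.77 for MINAP, 0.382 and 0.74 for PICANet. At d = 0.5 a single matched set has power of only 0.21.

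**A predicted-minus-not-predicted contrast**, with each Trust set against its own controls (variance 0.433² = 0.1875 per set):
- 2 v 3 Trusts: SE √[0.1875 × (1/2 + 1/3)] = 0.395, z = 2.53. Pooled z is 2.07 if the 2 respond (ratio 1.22) and 3.10 if the 3 respond.
- 1 v 2 PICUs: SE √[0.1875 × (1 + 1/2)] = 0.530, z = 1.89. Pooled z is 1.33 if the 1 responds and 2.67 if the 2 respond.

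The contrast therefore gains when few sites respond and loses when most do.

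**Phase-in.** Take a three-month ramp with weights 1/4, 2/4 and 3/4, then full effect. A step fitted to it recovers (0.25 + 0.50 + 0.75 + 9)/12 = 0.875 of the full effect. For a six-month ramp built the same way, a step recovers 0.75 and a three-month ramp recovers 0.89.

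**The case against.** **Pooling is not stated.** The article never says the matched sets are pooled, and counting data per intervention Trust leaves separate fits open. This stands as a limit on the claim. But clustering within hospitals is the language of a multi-hospital model, and nothing in the text promises an estimate for each Trust.

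**It is a feasibility study.** The CITS is to give preliminary evidence and is not a formal progression criterion. That lowers the stakes without removing them, because its result still informs whether a trial is justified and which audits it includes.

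**Stronger readings that the article does not support.**
- A reader might infer that unlike measures are averaged together. They are not: each outcome is modelled separately, the CMOC components are examined individually, and non-invasive ventilation is named as a measure not expected to change.
- A reader might infer that the study cannot test its context hypotheses. The case study also tests the CMO configurations, and the CITS results are then combined with it. The gap is in what the CITS contributes.
- A reader might infer that the ramp will be chosen to fit the outcomes. In simulation, taking the best ramp from 0 to 6 months raises a 5% type I error to about 8%, but no such search is described. Timing is to come from case-study reporting.
- A reader might want the predicted-minus-not-predicted contrast as the main test. It loses to pooling when 3 of 5 Trusts or 2 of 3 PICUs respond, its expected value is zero if all respond equally, and its gains assume that the predictions pick out the responders correctly.

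**Conclusion.** The point holds in limited form. The hypotheses are conditional on site, while the stated model names one intervention term per outcome and lets only the hospital's level vary. Read as one multi-hospital model, it recovers k/n of the effect in responding Trusts and gives the realist analysis no cross-site outcome pattern.

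The k/n result assumes equal-sized series, a common effect among responders and none elsewhere. The number of responders is illustrative, and the power figures also assume independent errors. Pooling remains the stronger analysis when most sites respond, so it should be supplemented and not replaced. The open phase-in is a prespecification weakness of modest size: a step fitted to a true three-month ramp loses about one eighth of the effect. Supplementary files 2 and 3 were not available and may settle some of this.

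**What to change.** 1. State whether the matched sets are pooled. Keep the pooled effect as a summary, and also estimate and report the intervention effect with its interval for every matched set (intervention Trust v its two controls): five for MINAP, three for PICANet. A random intervention effect is an alternative, though its variance will be poorly estimated from five or three sites.
2. Before post-period CITS data are opened, date and lock a Trust-by-measure record of where improvement is and is not expected, using pre-introduction information only. Set the matched-set estimates beside it. Treat any predicted v not predicted contrast as supportive.
3. Make the three-month linear phase-in the default in the analysis model, with case-study timing as a sensitivity analysis.

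The cost is a short dated table and a few model terms; no further data are needed. Single-Trust intervals will be wide (standard error about 0.43 residual SD, against 0.19 for the pooled MINAP effect, under independent errors). They should be read as estimates, and a wide interval at one Trust should not be taken as evidence of no effect there.

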### Setting/context

The feasibility study will be conducted in the five NHS acute Trusts in which the interview study that informed the design of QualDash was undertaken. Three Trusts are teaching hospitals that participate in both MINAP and PICANet and have been selected to ensure variation in key outcome measures (MINAP: 30-day mortality for patients hospitalised with ST-elevation myocardial infarction; PICANet: risk adjusted standardised mortality ratio). Two Trusts are DGHs that participate in MINAP but do not have a paediatric intensive care unit (PICU) and so do not participate in PICANet. These have been selected to ensure variation in the same key MINAP measure.

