### CITS study

Interrupted time series studies provide a robust method of assessing the effect of an intervention and have been used to assess effectiveness of a variety of complex interventions.^52^ In a CITS, the addition of a control group enhances causal inference because the presence of seasonal trends and other potential time-varying confounders can be assessed.^53^ Data will be collected across the five Trusts, with two control Trusts per intervention Trust, providing a total of 10 control Trusts. Control Trusts will be matched according to their size and outcomes pre intervention. Having more than one control site per intervention site increases power but, as the number of control sites per intervention site increases, quality of matching decreases. Therefore, we have chosen to have two control Trusts per intervention Trust to increase power while maintaining quality of the matching.

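### The hospital random intercept, and its fixed-effect check, leave serial correlation and hospital-specific shifts unmodelled, so intervals for the QualDash effect will be too narrow if either is present

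*Protocol article*

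**What the plan says.** All references are to the protocol article. Under CITS study, Analysis, each outcome is regressed on time and the intervention. Time enters as a quarterly seasonal effect and a linear trend. Dependence within hospitals is handled in one sentence, whose main provision is: "To account for clustering of monthly observations within hospitals, a random intercept will be fitted". The same sentence then names the only sensitivity analysis on this point, a fixed effect in place of the random one: "although a fixed effect for hospital as a sensitivity analysis will be explored". A gradual phase-in of the effect may be modelled. No other term or check for within-hospital correlation is named.

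On the amount of data, Sample size considerations says: "Monthly data will be obtained for 24 months pre-intervention and 12 months post-intervention". The CITS study section sets the comparison "with two control Trusts per intervention Trust, providing a total of 10 control Trusts". For PICANet, Setting/context says: "Three Trusts are teaching hospitals that participate in both MINAP and PICANet". The other two Trusts have no paediatric intensive care unit.

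**The concern.** A random intercept makes every pair of months in a hospital equally correlated, whether one month or 35 months apart. Given the intercept, months are independent. The fixed effect makes the same assumption, so agreement between the two analyses says nothing about whether it holds.

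The constant level that both remove largely cancels from a pre-to-post contrast anyway. The components that set the standard error of that contrast are serial correlation and a hospital's own shift between periods. The article gives reason to expect such shifts: its observation plan will follow local improvement initiatives and other contextual influences on the metrics.

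The stake is how far the CITS result can be trusted. Trial feasibility assessment and design places the CITS impact outside the formal progression criteria. It also says that the impact will be considered in judging whether a trial is justified, and that CITS data will inform the choice of audits, outcome variability and the length of the intervention period. Understated uncertainty would carry into those decisions.

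**Working it through.** **Inputs from the article.** 24 pre and 12 post months; 5 intervention and 10 control Trusts for MINAP; 3 intervention Trusts for PICANet. Six PICANet controls is an inference from the 2:1 rule. One hospital per Trust is taken.

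**The article's own count.** Per matched set, 24 × (1 + 2) = 72 points before and 12 × (1 + 2) = 36 after. Both agree with Sample size considerations. The power calculation is in a supplementary file that is not shown, so it was not checked.

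**Assumed inputs.** AR(1) correlation ρ, and SD τ of a hospital-specific pre-to-post shift, with residual SD set to 1. The article gives no value for either, so a range is used. The article does not write out the mean model, so two versions are used:
- Model A: hospital level, common trend, quarter, common post step, intervention × post.
- Model B: as A, with separate trends by group and separate level and slope changes.

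Hospital levels were entered as fixed. For this mainly within-hospital contrast the random-intercept standard error (SE) is taken as about the same.

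**SE if months are independent (Model A, MINAP).** Variance of one hospital's change in mean = 1/24 + 1/12 = 0.125. Multiply by (1/5 + 1/10) = 0.3: 0.0375, so SE = 0.194.

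**With ρ = 0.3.** The variance of a mean of n months is (1/n)[(1+ρ)/(1−ρ) − 2ρ(1−ρⁿ)/(n(1−ρ)²)].
- n = 24: 0.0753. n = 12: 0.1463.
- Covariance of the pre and post means: about [ρ/(1−ρ)²]/(24 × 12) = 0.0021.
- Variance of the change: 0.0753 + 0.1463 − 2 × 0.0021 = 0.217.
- Times 0.3: 0.0652, so true SE = 0.255.
- The SE the model reports is 0.191 on average, slightly under 0.194 because the fitted terms absorb some of the correlated variation.
- Ratio: 0.255/0.191 = 1.34. Type I error: 2[1 − Φ(1.96/1.34)] ≈ 14%.

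**With τ = 0.3 and ρ = 0.** Variance = 0.0375 + 0.3 × 0.3² = 0.0645, so true SE = 0.254. The reported SE is 0.195, the ratio 1.30 and type I error 13%.

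**Range (MINAP, 5 v 10): true SE/reported SE, with type I error of the nominal 5% test**

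| Assumption | Model A | Model B |
|---|---|---|
| ρ = 0, τ = 0 | 1.00; 5% | 1.00; 5% |
| ρ = 0.1 | 1.10; 7% | 1.08; 7% |
| ρ = 0.2 | 1.21; 10% | 1.17; 9% |
| ρ = 0.3 | 1.34; 14% | 1.26; 12% |
| ρ = 0.4 | 1.49; 19% | 1.37; 15% |
| τ = 0.3 alone | 1.30; 13% | 1.08; 7% |
| ρ = 0.3 and τ = 0.3 | 1.58; 21% | about 1.3; 14% |
| ρ = −0.2 | 0.83; 2% | 0.86; 2% |

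Dropping the common post step from Model A changes little (14% at ρ = 0.3). Results for 3 v 6 hospitals are almost identical.

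**The case against.** A reader might infer that the intervals simply are too narrow. The article does not support that. With no residual autocorrelation and no individual shifts the stated model is valid, and with negative autocorrelation its intervals are too wide.

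A reader might also infer that the plan ignores time structure. It does not: season, trend and matched controls remove shared sources of apparent serial correlation. But these act on the mean or the design, and correlation specific to one hospital can remain.

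The size depends on the mean model. With group-specific level and slope changes, the shift component alone falls to about 7%, close to nominal, while the autocorrelation component is reduced but persists. That limit stands.

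It can be said that error structure belongs in an analysis plan, which is not shown. Diagnostics often do. Here, however, the article names both the device for clustering of monthly observations and its sensitivity analysis, so the point concerns a stated choice. A fuller plan could still add to it.

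Finally, the CITS gives preliminary evidence, and the article states no decision rule based on a CITS p-value. This lowers the priority but does not remove the point.

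**Conclusion.** The concern holds conditionally. The stated model and its sensitivity analysis share one independence assumption, and the article names no step that would test it. Over the assumed range ρ = 0.1 to 0.4, type I error is about 7% to 19%, or 7% to 15% with group-specific level and slope changes. For τ = 0.3 alone it is about 7% to 13%, depending on the mean model. These figures rest on assumed ρ and τ, a normal approximation, balanced monthly data and, for PICANet, six controls.

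The change should be made, but the point does not invalidate the study: the CITS result is preliminary and outside the formal progression criteria. The article also gives no ground for dropping the fixed-effect analysis, which addresses a different assumption about hospital levels.

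**What to change.** In CITS study, Analysis:
- Keep the hospital random intercept and add AR(1) within-hospital residuals, with small-sample degrees of freedom (Kenward-Roger or Satterthwaite, where the software supports them for this error structure).
- Add a hospital-by-period random effect or random slope where it can be estimated. With nine PICANet hospitals this may fail, and within a single matched set of three it is barely estimable.
- Check and report residual autocorrelation.
- Add a cluster-level sensitivity analysis: one pre-to-post change per hospital, compared between groups by a t test on 15 − 2 = 13 df for MINAP and, if there are six controls, 9 − 2 = 7 df for PICANet. This applies to the pooled comparison; a single set of three would leave 1 df.
- Keep the fixed-effect sensitivity analysis if wanted, and state that it does not test independence of months.

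No new data are needed. The cost is revised wording, a few lines of R and probably wider intervals.
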